#### Secondary outcomes

The secondary outcomes measure the changes in TCM symptom scores, iron metabolism, hepcidin levels, and inflammatory factors. Spleen *Qi* deficiency syndrome is primarily characterized by poor appetite, fatigue, abdominal distension after meal or in the afternoon, and abnormal stool. The effectiveness of TCM is evaluated using the TCM syndrome score method (Table 3). According to the Standard Criteria for Syndrome Differentiation by TCM [11], a reduction in TCM syndrome score by ≥30% indicates that the clinical symptoms of spleen *Qi* deficiency either improved or disappeared and the treatment is considered clinically effective. The TCM syndrome score is calculated as follows: [(scores before treatment − scores after treatment) ÷ scores before treatment] × 100%. The indicators for iron metabolism are serum iron, total iron-binding capacity, SF, and soluble transferrin receptor. Inflammatory factors include interleukin (IL)-1, IL-6, and tumor necrosis factor (TNF)-α.

**Table 3 Tab3:** TCM syndrome scores for spleen *Qi* deficiency

Symptom	Score		
	Mild = 2	Moderate = 4	Severe = 6
Reduced food intake	No appetite, but maintain the original intake	Intake volume reduced by 1/3 compared before the onset of symptoms	Intake volume reduced by 2/3 compared before the onset of symptoms
Fatigue	Slightly tired and inactive but able to perform basic daily activities	Obvious sign of burnout, barely performing daily activities	Systemic weakness of the limbs, unable to perform daily activities
Bloating after meal	Slight abdominal distension, which can disappear within half an hour; is not severe; and does not require medications	Slight abdominal distension, which can disappear within mild; is not severe; and does not require medications	Abdominal distension cannot be improved within 2 h, affecting life, or taking ineffective medicines
Abnormal stool	Soft stools or slightly watery stools, piles are not formed, frequency of bowel movements: 2–3 times/day	Watery stools, loose stools, frequency of bowel movements: 4–5 times/day or 1–2 times/day	Loose stools, more than 3 times/day
Reduced talkativeness/responsiveness	Low energy, not interested to talk or respond	Mental fatigue, sleepy, not interested to engage in conversation	Extremely fatigued, idle
Absence of taste/ thirst	Occasional tasteless	Sometimes tasteless, reduced water intake	Persistent absence of taste, not thirsty all day long
Abdominal discomfort	Occasional or faint abdominal pain	Abdominal pain often occurs, lasting no more than 2 h	Abdominal pain is more obvious, lasting more than 2 h, or persistent
Nausea and vomiting	Occasionally nausea	Sometimes nausea, occasionally vomiting	Frequent nausea and vomiting
Excessive bowel gas	Occasional	Often	Hyperactive
Yellowish complexion	Yellowish complexion and reduced luster	Yellowish complexion and much reduced luster	Yellowish complexion and dull
Edema	Mild edema of the face or lower limbs	Edema of the face and limbs	Obvious body edema
Difficulty in Defecation	Straining to defecate	Require great effort to defecate	Hard to defecate or severely constipated

No symptom = 0

### Adverse event reporting

Details of the mild or severe adverse effects following TCM treatment would be recorded in the “case report form,” which comprise the time of occurrence, clinical manifestations, number of treatment elapsed days, duration, outcome, and possible side effects of the drug. Patients with abnormal laboratory test results must be followed up until the test results return to normal or to the level prior to the administration of medications; the clinicians shall determine whether the abnormalities are related to the treatment drug. If a serious adverse reaction develops, the “serious adverse event form” should be filled out, and the incident would be reported to the sponsor, research ethics committee, the Safety Supervision Department of National Medical Products Administration, and the Health Administration Department within 24 h. The sponsor and research ethics committee in charge will conduct the quality control and patient compliance assessment in this trial.

### Sample size considerations

Based on the sample size estimation formula (*n*1= *n*2 =2×[(μα+μβ)σ/δ]^2^+ μα^2^), the main research outcome indicator is the change in hemoglobin (Hb) levels, which will be used to estimate the sample size; compared with the baseline results, the Hb level of the experimental group (conventional medicine + YGS) increased to 20 g/L, while the Hb level of the control group (conventional medicine + placebo) increased to 14 g/L (standard deviation: 7 g/L, *n*1=group 1, *n*2= group 2, σ=14, δ=7, bilateral α=0.05, μα=1.96, unilateral β=0.2, μβ=0.84); therefore, each group should comprise 22 patients; considering a 30% loss due to follow-up, each group should comprise 30 patients. Therefore, we intend to recruit 60 patients from March 2020 to December 2021.

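### The sample size paragraph gives two incompatible input sets, and its printed formula gives 26 or 67 per group, not the stated 22

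*Protocol article*

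**What the plan says.** All the relevant text is in one sentence of the Protocol article, section Sample size considerations.

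- Endpoint: "the main research outcome indicator is the change in hemoglobin (Hb) levels".
- Expected results, in words: "the Hb level of the experimental group (conventional medicine + YGS) increased to 20 g/L", and "the Hb level of the control group (conventional medicine + placebo) increased to 14 g/L", with "standard deviation: 7 g/L". Since the outcome is a change, 20 and 14 g/L must be rises from baseline, so the difference is 6 g/L.
- Symbols, in the same parenthesis as the SD: "σ=14, δ=7, bilateral α=0.05, μα=1.96, unilateral β=0.2, μβ=0.84".
- Formula for each group: "2×[(μα+μβ)σ/δ]^2^+ μα^2".
- Result: "therefore, each group should comprise 22 patients; considering a 30% loss due to follow-up, each group should comprise 30 patients".

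**The concern.** In the printed formula σ is the standard deviation and δ the difference to be detected. The words give 7 and 6 for these, and the symbols give 14 and 7. The symbol values coincide with the control-group rise and the SD stated just before them. That suggests a labelling slip, but the article does not say so and no other section settles it.

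The two sets describe very different trials. The standardised difference is 6/7 = 0.86 under the first and 7/14 = 0.50 under the second. A reader of a null result needs to know which one the trial was sized for. The formula is a second, separate problem, because as printed it yields 22 from neither set. The allowance for loss is a third, smaller one.

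**Working it through.** **Inputs.** All come from Sample size considerations, except the 1:1 allocation, which is in Randomization and double-blind approach: μα = 1.96, μβ = 0.84, two-sided α = 0.05, power 80%. Set A (words): σ = 7, δ = 20 − 14 = 6. Set B (symbols): σ = 14, δ = 7.

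**Reproducing the stated 22.** The standard two-means formula, without the added term, is n = 2[(μα+μβ)σ/δ]².

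- Set A: 2 × (2.80 × 7/6)² = 21.34, rounded up to 22. This matches.
- Set B: 2 × (2.80 × 14/7)² = 62.72, rounded up to 63.

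**The formula as printed.** Add μα² = 1.96² = 3.84.

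- Set A: 21.34 + 3.84 = 25.18, rounded up to 26.
- Set B: 62.72 + 3.84 = 66.56, rounded up to 67.

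So 22 needs set A and removal of the added term.

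**Allowance for 30% loss.**

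- Dividing by the retained fraction: 22/0.7 = 31.4, so 32 per group.
- Multiplying up: 22 × 1.3 = 28.6, so 29 per group.
- The stated 30 covers the second but is 2 short of the first. If 30% of those enrolled are lost, 30 × 0.7 = 21 remain, one fewer than 22.

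**Power, two-sided 0.05.** The normal approximation is Φ[(δ/σ)√(n/2) − 1.96]. For set A at n = 22: (6/7)√11 = 2.843, and 2.843 − 1.96 = 0.883, giving 0.811. The t-test figures use the noncentral t distribution.

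| Per group | Set A, normal | Set A, t-test | Set B, normal | Set B, t-test |
|---|---|---|---|---|
| 21 | 79.3% | 77.4% | 36.7% | 35.3% |
| 22 | 81.1% | 79.3% | 38.2% | 36.7% |
| 30 | 91.3% | 90.4% | 49.1% | 47.8% |

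**The case against.** The strongest reply is that the intended calculation is easy to recognise. The means and SD given in words reproduce 22 exactly by the standard formula, with power within about one point of 80% at that number. On this view the symbol list is a slip and the added term an editing fault. As an account of what was probably intended, this stands. It does not make the printed calculation correct, because a reader who follows the symbols and formula as given arrives at 67.

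The added term might once have carried a fraction that was lost in typesetting or text extraction. With a factor of one quarter, set A would give 21.34 + 0.96 = 22.30, or 23 when rounded up. The article shows no such fraction, so this cannot be relied on, and it would not repair the σ and δ values.

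On loss, the shortfall depends on convention, since multiplying by 1.3 is satisfied by 30. The 21 evaluable is also a low case. The Statistical analyses section plans intention-to-treat as well as per-protocol analysis, with last observation carried forward, so between 21 and 30 per group could be analysed. The upper figure of about 90% is not assured either: carried-forward values may dilute the effect, and the randomization section removes unblinded cases from the statistics.

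A reader might go further and infer that the stated 80% power has no basis, or that the trial has only about a one-in-three chance of detecting its target effect. The document does not support either. The first overlooks that the inputs in words do give 22. The second requires an SD of 14 to be the real assumption, and nothing outside the symbol list supports that.

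**Conclusion.** The point holds as an internal contradiction that needs correcting. The SD and the difference are each stated twice with different values, and the printed formula gives 26 or 67 per group, never 22.

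The practical consequence depends on which inputs were meant:

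- With SD 7 and difference 6, the sample size is close to adequate. By t-test, power is about 79% at 22 per group and 77% at the 21 left after 30% loss. It rises to about 90% if all 30 are analysed with no dilution of the effect. The worst gap from the 80% target is about 3 points.
- With σ = 14 and δ = 7, the trial is seriously underpowered: by t-test 35% at 21 per group, 37% at 22 and 48% at 30.

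The first is the more plausible reading, because it is the only one that leads to 22, but the sponsor has to confirm it. These power figures assume a two-group comparison of mean change with equal SDs.

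**What to change.** Keep 60 patients. The sponsor confirms which inputs were intended and rewrites the paragraph to match.

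- **If SD 7 and difference 6:** replace the symbol values with σ = 7 and δ = 6. Delete the added μα² term, so that the formula yields the stated 22. Say that hemoglobin increased by 20 and 14 g/L, rather than to those levels. State that 30 per group with 30% loss leaves 21 evaluable and about 77% power by t-test.
- **If σ = 14 and δ = 7:** correct the means and SD given in words, and restate the power as about 35% at 21 per group and 48% at 30.

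Introducing a quarter-term correction and a target of 23 evaluable is not advisable. The article contains no such term, and 23/0.7 = 32.9, so 33 per group would be needed and the planned 30 would miss the new target.

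The cost is one reworded paragraph and no extra patients. The stated power becomes slightly less favourable in the first case and much less so in the second.

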### Randomization and double-blind approach

Participants who met the inclusion criteria and signed an informed consent form would be allocated to a group (Fig. 1). Based on a stratified block randomization design with a 1:1 ratio, two groups of patients would be assigned by the study center at the time of study. Allocation of patients is based on the random numbers (1 to 60) generated using an SPSS software version 25.0, and patient’s details are saved and kept in a sealed envelope by an independent clinical statistician based on the double-blind research method. In the study, the procedures of generating random numbers, evaluating the results of primary and secondary outcomes, and statistical analysis are independently performed by dedicated personnel who are blinded to outcome data. Upon completion of the study and data analysis, the efficacy and safety of YGS treatment shall be evaluated. During the clinical trial period, the treatment regimen of both study groups would be managed by their respective study center/hospital according to the approved treatment plan. If a patient develops a serious adverse reaction or life-threatening condition during the course of clinical trial, the clinician responsible for the patient must provide the best on-site medical care. Simultaneously, the clinician must immediately report the incidence to the inspector, upon which the letter containing patient’s treatment grouping information needs to be opened to break the blind, and the type of drug used is identified to ensure that the patient is provided with the appropriate emergency medical assistance. Once a blind is uncovered, the case would be regarded as a shedding case and would be excluded from the statistics, and any occurrence of adverse reactions would be recorded.

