YGS is an oral concoction first reported in the Pediatric Medicine Card Straight Tactic, a famous classical book of TCM written approximately 900 years ago. YGS is known for its functions of tonifying the splenic *Qi* and gasification stagnation. YGS has been traditionally used in Korea to treat a variety of inflammatory diseases; pretreatment with YGS inhibited the production of TNF-α훼 and IL-6 in LPS-stimulated mouse peritoneal macrophages [16], which is consistent with our previous animal experiment results [7], indicating the confirmed inhibitory effect of YGS on inflammatory factors. In our current study, we intend to enroll patients with MDS anemia who are not dependent on blood transfusion and provide them with relevant treatments during the early stages of lower-risk MDS. In patients with lower-risk MDS, early T cell function is increased, and inflammatory factors are highly expressed [17], which is the same as the pathological process of iron metabolism in ACD. Therefore, based on a previous study, we hypothesized that YGS can regulate iron metabolism by reducing the inflammatory factors of lower-risk MDS, thereby improving anemia. We intend to include 60 patients with lower-risk MDS anemia; conduct a randomized, double-blind, placebo-controlled parallel trial; administer oral YGS granules or placebo granules to included patients; and evaluate the clinical efficacy of this treatment.

This trial has the following advantages: (1) This study is a randomized, double-blind, placebo-controlled, multicenter study that is scientific and rigorous. (2) At present, no relevant research has evaluated the effects of TCM on inflammatory factors and iron metabolism in MDS. The findings of this study would fill this gap of knowledge in the literature. This study has certain limitations. It only evaluates the early stages of MDS; most of the patients with MDS are already on the late stages when they see a doctor. Therefore, it might be difficult to recruit patients, and we have to set the sample size based on the minimum number of cases required for statistical analyses. In this study, MDS treatment using Western medicine is also recorded as an individualized treatment regimen, which would be further analyzed as a stratified group of results in our statistical analyses.

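### Enrolling 30 per group does not deliver the stated 30% loss allowance on 22: at that loss 21 remain, a minor shortfall of one patient per group

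*Protocol article*

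**What the plan says.** All three figures stand in one sentence of the protocol article, Sample size considerations: "therefore, each group should comprise 22 patients; considering a 30% loss due to follow-up, each group should comprise 30 patients". The total follows from it: "we intend to recruit 60 patients from March 2020 to December 2021". The error rates are given as "bilateral α=0.05, μα=1.96, unilateral β=0.2, μβ=0.84", so the 22 is meant to carry 80% power at a two-sided 5% level. The section gives no formula for the step from 22 to 30.

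The same section gives the inputs behind the 22 in two ways. In words, the expected haemoglobin changes are 20 and 14 g/L (a difference of 6) with an SD of 7 g/L. In symbols, σ=14 and δ=7. The printed formula also adds a μα² term.

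Statistical analyses plans both intention-to-treat and per-protocol analyses and allows last observation carried forward for missing data. Randomization and double-blind approach removes from the analysis any patient whose blind is broken.

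**The concern.** The 30 is offered as the number that protects 22 against a 30% loss. A reader will therefore take it that 60 patients can lose 30% and still retain the number on which the 80% power was based. If 30% of 30 are lost, the number left is below 22. The loss the trial can absorb is then overstated, and the power at the planned loss is lower than the section implies. The size of that effect decides how much weight the point deserves.

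**Working it through.** **Inputs** (all from Sample size considerations): 22 per group before allowance; loss 30%; 30 per group enrolled; z-values 1.96 and 0.84; difference 6 g/L and SD 7 g/L in words; σ=14 and δ=7 in symbols.

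**1. Where the 22 comes from.** Without the μα² term, n = 2 × [(1.96 + 0.84) × SD/difference]².

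- SD 7, difference 6: 2 × (2.80 × 7/6)² = 21.34, rounded up to 22. This reproduces the plan.
- The same with the printed term: 21.34 + 1.96² = 25.18, rounded up to 26.
- σ=14, δ=7: 2 × (2.80 × 14/7)² = 62.72, rounded up to 63. With the term, 66.56, rounded up to 67.

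So the 22 corresponds to the inputs given in words with the added term left out.

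**2. From 22 to the enrolled number.**

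- Dividing by the retained fraction: 22/(1 − 0.30) = 31.43, so 32 per group, 64 in total.
- Adding 30%: 22 × 1.30 = 28.6, so 29 per group.
- Starting from the unrounded base: 21.34/0.70 = 30.49, so 31 when rounded up. It gives 30 only when rounded to nearest.

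None of these, rounded up, gives 30.

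**3. From 30 back to the number left.** 30 × (1 − 0.30) = 21. This is below 22, and also below the unrounded 21.34. Keeping 22 of 30 allows at most 8 losses: 8/30 = 26.7%.

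**4. Effect on power** (two-sided 5%). The normal approximation is Φ(difference/(SD × √(2/n)) − 1.96). The t-test column uses the noncentral t distribution.

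| Inputs | n per group | t-test | Normal approximation |
|---|---|---|---|
| difference 6, SD 7 | 22 | 79.3% | 81.1% |
| difference 6, SD 7 | 21 | 77.3% | 79.3% |
| δ=7, σ=14 | 22 | 36.7% | 38.2% |
| δ=7, σ=14 | 21 | 35.3% | 36.7% |

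With difference 6 and SD 7, losing one patient per group costs 79.3 − 77.3 = 2.0 points by t-test and 81.1 − 79.3 = 1.8 points by normal approximation. Under the other pair of inputs it costs about 1.4 to 1.5 points. Which pair is used matters far more than the step from 22 to 21.

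**The case against.** The best defence is that this is loose rounding. The section prints no inflation formula; adding 30% gives 28.6, and 30 is a round number above it; the unrounded base over 0.70 is 30.49, which is 30 to the nearest whole number. That explains how the 30 may have arisen, but on neither route do 22 remain after a 30% loss.

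Second, intention-to-treat with last observation carried forward may keep some lost patients in the analysis, since blood is taken at months 1, 2 and 3. This stands in part. A reader might infer that every analysis falls to 21 per group, and the protocol does not support that: the 21 applies most directly to the per-protocol set. Yet a carried-forward value is not a full observation, the article says only that the method can be used, and unblinded cases are excluded. The authors themselves inflated for loss, so they treated 22 as the number wanted after it.

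Third, a reader might infer that the inflation step is what takes power below 80%. By t-test it is not: with difference 6 and SD 7, power at 22 is already 79.3% before any loss.

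Fourth, a reader might infer that the plan rules out any reserve, because the Discussion says "we have to set the sample size based on the minimum number of cases required for statistical analyses" and the allocation list is described as "Allocation of patients is based on the random numbers (1 to 60) generated using an SPSS software version 25.0". The first remark explains difficulty in recruiting and says nothing about the loss allowance. The second only restates a total of 60. Neither adds to the arithmetic.

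**Conclusion.** The point holds as a minor arithmetic error. As printed, 30 per group does not keep 22 at a 30% loss: it keeps 21, and 32 per group (64 in total) would be needed. Nothing elsewhere in the article changes the 22, the 30% or the 30.

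The count takes lost patients as not fully observed. The cost of about 2 power points assumes a difference of 6 g/L and SD 7 g/L. The step from 22 to 30 is wrong whichever inputs produced the 22, but any power figure attached to 21 depends on them, and the article leaves them in conflict.

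It would go too far to conclude from this step alone that the trial is materially underpowered, or that 64 patients would put the sample size right. Moving from 30 to 32 per group would leave the conflict between the two sets of inputs untouched, and that conflict is the larger problem in the same section.

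**What to change.** Keep 60 patients and correct the sample size section in this order.

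1. Reconcile the SD, the difference and the formula behind the 22: SD 7 with difference 6, or σ=14 with δ=7, and with or without the μα² term. Until that is done, 22 should not be called the required number.
2. State that 30 per group with 30% loss leaves 21 evaluable, and that 22 remain only if at most 8 of 30 (26.7%) are lost.
3. Give the power at 21 per group under the reconciled inputs. By t-test this is about 77% with difference 6 and SD 7, and about 35% with σ=14 and δ=7.
4. Use n/(1 − loss) for any inflation, applied to whatever number step 1 yields.

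The assumed loss should not simply be lowered to 26% so that 30 fits; that would be back-calculation unless there is evidence for it.

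For the loss step, the cost is one rewritten sentence, with no added patients and no change to the allocation list or the analysis. The stated loss tolerance or power becomes slightly less favourable. Step 1 may show a larger problem with the sample size, but that would come from the inputs and not from this correction.

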### Statistical analyses

A descriptive statistical analysis of all the quantified variables in this study would be performed. The mean, median, and standard deviation will be calculated for quantitative variables, while the absolute and relative frequencies will be calculated for qualitative variables. The SPSS software (version 25.0; IBM Inc., USA) would be used for data processing and analysis. Statistical analysis would be based on the intention-to-treat and per-protocol population principles. The missing data can be processed using the last observation carried forward method. To compare the changes in TCM symptom scores and hematological data of patients before and after taking intervention treatment, multiple comparisons would be performed. A repeat measurement data analysis of variance will be initially conducted followed by a separate effect analysis, including comparisons between groups at each time point, using a multivariate logistic regression model to analyze the correlation between iron metabolism, hepcidin levels, and IL-6, TNF-α, IL-1 expression changes, and curative effect. Additionally, a subgroup analysis can be performed according to the R-IPI, and covariance analysis can be performed considering the factors such as age and sex. A two-sided *P* value of < 0.05 is considered significant.

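### LOCF is the only missing-data method named, although the protocol plans 30% loss and expects haemoglobin to rise, so its no-change assumption contradicts the protocol's own figures

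*Protocol article*

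**What the plan says.** Protocol article, Statistical analyses: "The missing data can be processed using the last observation carried forward method". The analysis follows intention-to-treat and per-protocol principles. It uses a repeated-measures analysis of variance, followed by comparisons between groups at each time point.

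Sample size considerations: "compared with the baseline results, the Hb level of the experimental group (conventional medicine + YGS) increased to 20 g/L", and the control group ("conventional medicine + placebo) increased to 14 g/L (standard deviation: 7 g/L"). Read as changes from baseline, these are rises of 20 and 14 g/L, a difference of 6 g/L. The same sentence also prints "σ=14, δ=7, bilateral α=0.05", a second SD and difference. It arrives at 22 patients per group and then says "considering a 30% loss due to follow-up, each group should comprise 30 patients".

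Data collection: blood is taken before treatment and at months 1, 2 and 3. Primary outcome: Hb compared with baseline, with a rise of 10 g/L counted as effective.

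**The concern.** LOCF gives a dropout the month-3 value that would apply if Hb had stopped moving at the last visit. The protocol expects the opposite in both arms. Someone last seen at baseline is given a change of zero and counts automatically as a non-responder on the 10 g/L criterion. On a straight-line path the mean change at month 1 is only 20/3 = 6.7 g/L (YGS) or 14/3 = 4.7 g/L (placebo).

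The sample size section treats the 30% as patients whose information is lost, and recruits extra patients to cover them. LOCF puts those patients back into the analysis with understated changes. If the two arms lose similar proportions, the effect is diluted. If they lose different proportions, the loss itself creates a difference between arms.

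**Working it through.** **Inputs from the protocol article.** Rises of 20 and 14 g/L, SD 7 g/L, two-sided α 0.05, β 0.2, 30 per arm, 30% loss (Sample size considerations); visits at baseline and months 1, 2 and 3 (Data collection).

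**Assumptions not settled by the article.**
- SD 7 is used, although 14 is also printed.
- Hb path: linear (1/3, 2/3 and all of the rise at months 1, 2 and 3), early plateau (70/90/100%) or late (10/40/100%).
- Dropouts were last seen evenly at baseline, month 1 and month 2 (B–2), or evenly at months 1 and 2 only (1–2).
- Dropout is independent of outcome.
- Between-visit correlation is 0.5; 0.7 gives nearly the same results.

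**The plan's own figure.** 2 × [(1.96 + 0.84) × 7/6]² = 21.34, so 22 per arm, as stated. This leaves out the μα² term printed in the formula. Allowing for 30% loss gives 22/0.7 = 31.4 or 22 × 1.3 = 28.6; the stated 30 lies between. From 30, a 30% loss leaves 21 completers.

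**Expected LOCF mean.** Let m be the full rise in an arm, d the proportion lost, and f the average fraction of the rise reached at a dropout's last visit. The expected LOCF mean change is m × (1 − d + d × f).

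*Equal loss.* The estimated difference is 6 × (0.7 + 0.3f). In the linear B–2 case, f = (0 + 1/3 + 2/3)/3 = 1/3, giving 6 × 0.8 = 4.8 g/L.

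*No true effect, unequal loss.* The false difference is m × (gap in loss) × (1 − f). In the linear B–2 case with m = 14 and 20% versus 40% loss, it is 14 × 0.2 × 2/3 = 1.9 g/L.

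Power and type I error below come from 20,000 simulated trials per scenario, using a two-sided t-test on month-3 change.

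| Path, last visit | f | LOCF estimate at 30%/30% loss (true 6.0) | LOCF power | Type I error, both arms +14, 20% vs 40% loss |
|---|---|---|---|---|
| Linear, B–2 | 0.33 | 4.8 | 54% | 14% |
| Linear, 1–2 | 0.50 | 5.1 | 66% | 11% |
| Early plateau, B–2 | 0.53 | 5.2 | 64% | 10% |
| Early plateau, 1–2 | 0.80 | 5.6 | 84% | 6% |
| Late, B–2 | 0.17 | 4.5 | 44% | 18% |
| Late, 1–2 | 0.25 | 4.6 | 48% | 16% |

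Completers in the same data give 6.0 g/L, power of about 76% and type I error near 5%. With equal loss and no true effect, LOCF also stays near 5% in every row.

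**True effect, unequal loss (linear, B–2).** Each arm keeps 1 − d × 2/3 of its rise.
- YGS loses 20%, placebo 40%: 20 × 0.867 − 14 × 0.733 = 17.33 − 10.27 = 7.1 g/L.
- YGS loses 40%, placebo 20%: 20 × 0.733 − 14 × 0.867 = 14.67 − 12.13 = 2.5 g/L.

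**Sensitivity of the type I figure.** With 25% versus 35% loss and both arms at +14, it is about 5% to 8%. With SD 14, the linear B–2 figure at 20% versus 40% loss falls from 14% to about 8%.

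**The case against.** The article says only that missing data can be handled this way, which is permissive. It plans a per-protocol analysis beside intention-to-treat, and a fuller plan may exist. All true, but the point is not that further methods are missing. The one method that is named conflicts with the design assumptions printed beside it.

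The size of the harm rests on a path and dropout timing that the article does not state. This stands, and it is why ranges are given. In the early-plateau case with every patient seen at least once after baseline, LOCF has more power than the completers (84% against about 76%), so a loss of power is likely but not certain.

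Three stronger readings are tempting and are not supported:
- *LOCF inflates false positives in the trial as planned.* The protocol applies one 30% allowance to both arms, and equal loss leaves type I error near 5%. The placebo is matched for packaging, weight, odour and colour. Taste is not listed, so differential loss is possible but not shown.
- *LOCF always shrinks the effect.* It does so when loss is similar. If placebo loses more, it can enlarge the effect.
- *Treating filled-in values as observed spoils the test.* No such consequence appears: type I error under equal loss is nominal.

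Completers are an unbiased benchmark here only because simulated dropout was independent of outcome. They are not offered as the remedy.

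**Conclusion.** The concern holds in this limited form. LOCF as the only named method contradicts the protocol's expectation of rising Hb, at a planned loss large enough to matter. With equal 30% loss at SD 7, the planned 6.0 g/L is understated by about 0.4 to 1.5 g/L. Power falls below that of the completers in five of the six scenarios. A raised type I error, about 6% to 18%, depends on unequal loss (20% versus 40%), no true effect and a 14 g/L rise in both arms; it is lower at SD 14 or with a smaller imbalance. The direction under equal loss is firm. The exact figures depend on the assumptions listed, and the two printed SDs need to be reconciled as a separate matter.

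**What to change.** Make the main Hb analysis a likelihood-based mixed model for repeated measures on all observed Hb values, with visit, arm by visit and an unstructured covariance, and report the arm difference at month 3. Keep baseline Hb in the outcome vector with a mean common to both arms. If baseline is only a covariate, patients with no post-baseline Hb drop out, which departs from the intention-to-treat principle. Multiple imputation that retains those patients is an acceptable alternative. Keep LOCF as a sensitivity analysis at most.

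The cost is analysis wording. The visits are already scheduled, the model serves the same repeated-measures aim, and the named software can fit it. The article reports 19 patients recruited at submission, so the change could be fixed before unblinding. The downside is reliance on missing-at-random, which dropout for lack of effect could violate. Add one sensitivity analysis for data missing not at random, for example by shifting the imputed month-3 values of dropouts over a prespecified range, separately by arm.
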